**Methods/design:**

The PORTAL trial is a multicenter randomized controlled, patient-blinded, parallel-group, phase III non-inferiority trial performed in seven high-volume centers for pancreatic and robotic surgery in China (> 20 RPD and > 100 OPD annually in each participating center). The trial is designed to enroll and randomly assign 244 patients with an indication for elective pancreatoduodenectomy for malignant periampullary and pancreatic lesions, as well as premalignant and symptomatic benign periampullary and pancreatic disease. The primary outcome is time to functional recovery postoperatively, measured in days. Secondary outcomes include postoperative morbidity and mortality, as well as perioperative costs. A sub-cohort of 128 patients with pancreatic adenocarcinoma (PDAC) will also be compared to assess the percentage of patients who undergo postoperative adjuvant chemotherapy within 8 weeks, in each arm. Secondary outcomes in this cohort will include patterns of disease recurrence, recurrence-free survival, and overall survival.

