### Inclusion and exclusion criteria

The inclusion criteria for trial eligibility are [1] age ≥ 18 years [2]; clinical indication for pancreatoduodenectomy [3]; patient eligibility for both RPD and OPD [4]; patient performance status of 0 or 1 based on comorbidities, assessed using the Karnofsky score and the Nutritional Risk Screening Tool (NRS-2002) score; and [5] imaging with computed tomography (CT) and/or MRI pancreas performed within 8 weeks for benign and 4 weeks for malignant disease; for the latter, tumor staging with MRI liver, CT chest, and cancer antigen 19-9 (CA19-9) is also mandatory not earlier than 4 weeks prior to surgery.

The exclusion criteria are [1] body mass index > 35 kg/m^2^, [2] pregnancy, [3] previous history of major abdominal surgery, [4] requirement for multivisceral resection (additional surgical resection of surrounding solid organs), [5] ongoing treatment for other primary malignancy, [6] preoperative chemotherapy and/or radiotherapy in patients with pancreatic adenocarcinoma, and [7] involvement of major regional vessels by the tumor (portal and superior mesenteric vein, superior mesenteric artery, hepatic artery, celiac artery) as defined by the borderline resectable and locally advanced nomenclature [16].

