### Analysis of long-term outcomes in patients with pancreatic adenocarcinoma

The sub-cohort of patients with PDAC in the two arms will be followed up for a period of 2 years after surgery, or until their time of death within this period. During that time, the administration and type of systemic therapy will be documented; the main focus will be the recurrence-free survival (RFS) and overall survival (OS), defined as the time from surgery to the first radiological evidence of disease recurrence and death, respectively.

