### Data collection and patient follow-up

At the time of patient consent for participation in the trial and prior to randomization, baseline patient characteristics will be recorded. These will mainly comprise demographics (age, sex, BMI) and past medical history, including comorbidities for the assessment of performance status. Clinical presentation will also be documented with a focus on patient symptoms and signs; in cases of solid tumors, imaging data will also be collected and evaluated: tumor size and staging, vessel involvement, and pancreatic duct (PD) diameter, as well as the presence of preoperative biliary drainage and treatment with somatostatin analogs. At the time of surgery, the pancreatic texture will be documented (soft versus hard gland) and the PD diameter will be also measured. Previously discussed minor variations in operative approach and anastomotic reconstruction will be added in patient record forms. Regarding the quality of life assessment, patients will complete the latest translated version of the EuroQoL EQ-5D-5 L questionnaire, which is a self-reported assay focusing on five parameters: pain/discomfort, anxiety/depression, usual activities, self-care, and mobility. Each of these parameters is scored from 0 to 5 (no issue, slight problem, moderate problem, severe problem, unable). Patients also score independently their health status on a scale numbered from 0 to 100: 100 meaning the best health they can imagine, and 0 the worst. The questionnaires will be filled and collected by medical or nursing staff on postoperative days 1, 3, 5, and 7 during the patients’ hospital stay; further questionnaires will be completed in the postoperative setting every week until day 30, every month until day 90, and every 3 months until 12 months, when the evaluation will terminate (Fig. 3). Remote completion will take place via telephone communication, by mail, or face-to-face for all patients who are followed up at the participating centers. Furthermore, in the postoperative setting, primary and secondary outcomes during the hospital stay will be documented daily by the trial coordinators. Patients will be further followed up after discharge with out-patient clinic appointments or via telephone/video conference as an alternative to monitor for delayed postoperative complications, quality of life changes, and disease recurrence patterns. Frequent communication and close monitoring of enrolled patients by the participating centers via telephone and mail will aim to promote patient retention during the trial period. All collected data are de-identified and stored safely in a centralized online database, which is accessible by all participating institutions for data input. The stored data are not available to individual collaborators and are only screened by two dedicated members of the trial team for assessment of wrong or missing data. Data processing regarding the results is conducted by a group of two independent statisticians who work under the data monitoring committee.

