### Statistical considerations and analysis

The main hypothesis in the PORTAL trial is that functional recovery of patients who undergo RPD is non-inferior to the one of patients who undergo OPD. Based on institutional historical data and information from retrospective series in the literature, the time to functional recovery in OPD is 10 days with a standard deviation of 2.5 days. Non-inferiority of functional recovery in RPD will be assessed with a non-inferiority (*δ*) margin of 10% or 1 day. With a one-sided test, a significance level of 5% (*α* = 0.05), and a power (1 − *β*) of 80%, the cohort for the trial is calculated to 200 patients (per-protocol (PP) group), using the PASS 11.0 software (NCSS, Kaysville, UT, USA) with a sample allocation ratio of 1:1 between the RPD and OPD groups. However, we anticipate a conversion rate in the RPD group of 10%, 3% incidence of occult abdominal metastatic disease in both groups, and 5% of patients to be lost to follow-up. Therefore, the final cohort will include 122 patients in each arm (intention-to-treat (ITT), Fig. 1). The main analysis will be conducted on the ITT group according to the randomized initial assignment of patients in each study arm at baseline. All enrolled patients from the ITT population who do not fulfill the aforementioned protocol violations will be included in the PP group. Additionally, patient characteristics of those who will be excluded from the PP analysis will be separately evaluated. Non-inferiority will be concluded if the lower bound of the 95% confidence interval (CI) for the difference between the two groups in time to functional recovery is not lower than − 1 day of the non-inferiority margin.

A second primary endpoint of the study is the percentage of patients with a diagnosis of pancreatic adenocarcinoma in each study arm, who will be fit for the initiation of postoperative adjuvant chemotherapy 8 weeks after the day of surgery. Institutional empirical data demonstrate that 50% and 75% of patients who undergo OPD and RPD, respectively, are eligible for adjuvant chemotherapy at 8 weeks, which is considered the optimal time for postoperative systemic treatment. With the same power and significance level as in the ITT group, 64 patients with pancreatic adenocarcinoma will be included in each arm to assess for the superiority of RPD.

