Primary and secondary outcome data for both ITT and PP groups will be compared utilizing appropriate statistical methodology. Categorical variables will be represented as frequency and proportion and will be analyzed using Fisher’s exact or chi-square tests, as appropriate. Continuous variables will be presented as mean values with standard deviation (SD), or median values with interquartile range (IQR), and will be compared using the two-sample *t*-test or Mann-Whitney *U* test, as per the type of distribution. A logistic regression analysis was performed for consideration of randomization stratification, based on the predetermined parameters. Survival of patients with pancreatic adenocarcinoma between the two arms will be estimated using the Kaplan-Meier analysis method and compared between the groups with the log-rank test. The SAS software v. 9.2 (SAS Institute Inc., USA) was utilized for all statistical analyses.

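### The PDAC survival comparison is fixed as an unadjusted log-rank test although baseline CA19-9 and imaging tumour size are available: a valid test, but a cheap gain in efficiency is left unused

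*Protocol article*

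**What the plan says.** - **Survival method.** Protocol article, Statistical considerations and analysis: survival in PDAC is "estimated using the Kaplan-Meier analysis method and compared between the groups with the log-rank test". No covariates, strata or Cox model are named for it. The only model in that section is a logistic regression on the stratification parameters, which is not a survival model.
- **Role of the outcomes.** The section on long-term outcomes in PDAC says of the two-year follow-up that "the main focus will be the recurrence-free survival (RFS) and overall survival (OS"). The abstract and Table 2 list both as secondary. The Discussion nevertheless expects the PDAC analysis to settle the question of long-term oncological outcomes after RPD.
- **Size.** "64 patients with pancreatic adenocarcinoma will be included in each arm to assess for the superiority of RPD". This number is set by the chemotherapy endpoint. No survival event count, hazard ratio or power is given.
- **Baseline measures of tumour burden.** Under Inclusion and exclusion criteria, for malignant disease, "tumor staging with MRI liver, CT chest, and cancer antigen 19-9 (CA19-9) is also mandatory not earlier than 4 weeks prior to surgery". Under Data collection and patient follow-up, for solid tumours, "imaging data will also be collected and evaluated: tumor size and staging". That section places the baseline record before randomisation.
- **Stratification.** The Randomization process section names fistula risk, endoscopic biliary stenting and PDAC diagnosis. Within PDAC only the first two vary, and neither measures tumour burden.

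**The concern.** A small survival comparison will be read for oncological harm or benefit of the robotic approach. Measures of tumour burden taken before randomisation are available, but the one comparison named does not use them. If they are prognostic, leaving them out gives up power. It also leaves any visible baseline imbalance to be argued over afterwards, when a choice of adjustment would be post hoc. There is a specific trap as well. Tumour size is recorded twice, once on baseline imaging and once among the pathology findings in the secondary outcomes, so a late adjustment could pick up the post-randomisation value.

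**Working it through.** **1. The plan's own figure.** Inputs: 50% against 75% and 80% power, from Statistical considerations and analysis.

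n = [z(α)·√(2·p̄·q̄) + z(β)·√(p₁q₁ + p₂q₂)]² / (p₂ − p₁)², with p̄ = 0.625.

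- Two-sided 5%: (1.960 × 0.6847 + 0.8416 × 0.6614)² / 0.0625 = (1.3420 + 0.5567)² / 0.0625 = 57.7, so 58. Dividing by 1 − 0.08 (3% occult metastases plus 5% loss) gives 63.04, so 64.
- Exact two-sided Fisher power at 64 per arm is 80.2%.

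So 64 per arm reproduces as a two-sided calculation. The one-sided 5% that the section states for the main endpoint would give 46; that mismatch is a separate matter. What counts here is that 64 sizes the chemotherapy comparison, not survival.

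**2. What 128 patients give for survival.** The event count is not in the article, so it is assumed: 64 events (half of 128) and 102 (about 80%). Two-sided 5% is also assumed.

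Power = Φ(½·√d·|ln HR| − 1.960). For d = 64 and HR 0.6: ½ × 8 × 0.5108 − 1.960 = 0.083, and Φ = 53%.

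| Events | HR 0.6 | HR 0.7 | HR detectable at 80% power |
|---|---|---|---|
| 64 | 53% | 30% | 0.50 |
| 102 | 73% | 44% | 0.57 |

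HR 0.7 at 80% power needs 4 × (1.960 + 0.8416)² / (ln 0.7)² = 247 events, more than the 128 patients.

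**3. Log-rank against adjusted Cox.** Simulation with 64 per arm, exponential survival, control median 22 months, censoring at 24 months, two independent standard-normal baseline covariates of equal strength, two-sided 5% and 2,000 runs per row. All survival inputs are assumptions. The treatment HR is 0.6, holding the covariates fixed.

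| Covariate HR per SD (each) | Mean events | Log-rank | Adjusted Cox | Difference (points) |
|---|---|---|---|---|
| 1.0 (not prognostic) | 57 | 49.6% | 49.1% | −0.5 |
| 1.3 | 58 | 46.1% | 47.7% | +1.6 |
| 1.5 | 59 | 44.7% | 51.0% | +6.3 |
| 2.0 | 61 | 34.0% | 51.5% | +17.5 |

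The simulation error of each power figure is about √(0.5 × 0.5 / 2,000) = 1.1 points, so the first two rows show little or no difference. The model simulated has three terms. The fix below has five (arm plus four covariates), which with 57 events leaves 57 / 5 ≈ 11 events per term.

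**4. Validity.** With a true HR of 1.0 and the same covariate strengths, the false-positive rate is 4.6% to 5.5% for the log-rank test and 4.3% to 5.6% for the adjusted model. Both are at the nominal level.

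**5. Chance imbalance.** For one standardised covariate, the SD of the difference between arms is √(2/64) = 0.177. The probability of a difference above 0.25 SD in either direction is 2 × [1 − Φ(0.25 / 0.177)] = 2 × [1 − Φ(1.414)] ≈ 16%.

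**The case against.** The case against has real force.

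- **Nothing is stated wrongly.** An unadjusted log-rank test is valid after 1:1 randomisation, and step 4 confirms it. This stands, and it is why the point is not an error.
- **It may belong to the SAP.** The SAP was not available, and the article does not exclude an adjusted analysis. The absence of a covariate list would be no finding. The point rests only on the method that the article does name, and it falls away if the SAP already adds the model.
- **The outcomes are secondary and unpowered.** This stands. The main-focus wording describes the follow-up period, not a rank among the hypotheses. Eligibility is also limited to upfront resectable disease, which may narrow the prognostic spread.

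Three stronger readings are tempting, and the documents do not support them.

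- *That the trial ignores its strongest prognostic factors.* The article nowhere says how prognostic CA19-9 or tumour size is, and the gain depends wholly on that. Nor is tumour size mandatory: CA19-9 and staging are, while size is listed among the imaging data collected.
- *That the log-rank test has an inflated false-positive rate.* Among simulated trials with an imbalance above 0.25 SD (about 16% of them), in a one-covariate simulation with assumed log-hazard effects of 0.3 to 0.7 per SD, the rate is 7.3% to 8.9%. Overall it is 4% to 5%, so the other 84% must run lower: between (4 − 0.16 × 8.9) / 0.84 = 3.1% and (5 − 0.16 × 7.3) / 0.84 = 4.6%. The test is calibrated, and quoting only the imbalanced trials misleads.
- *That the unadjusted analysis biases the hazard ratio toward 1.* The attenuation is the difference between a marginal and a conditional hazard ratio. It is not a bias of the log-rank test, and the article specifies no hazard ratio.

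**Conclusion.** The point holds as an efficiency and robustness weakness in secondary outcomes. At a treatment HR of 0.6, adjustment changes power by about 0 points if the covariates are not prognostic and by up to about 17.5 points if both are strong (HR 2.0 per SD). The range rests on assumptions that the article cannot settle: the control median, the event count, two-sided testing, the prognostic strength, and independent covariates with a log-linear effect. The trade is lopsided in favour of adjusting, since almost nothing is lost when the covariates turn out uninformative. It does not rescue the comparison: in these scenarios adjusted power stays near 50%, and moderate effects remain out of reach with 128 patients. A reader should not infer that the planned test is invalid or its result biased. Label: cheap improvement.

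**What to change.** Pre-specify, for OS and for RFS in PDAC, a Cox model by randomised arm adjusted for:

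- log CA19-9, pre-randomisation value;
- tumour size on baseline imaging, explicitly not specimen size;
- the stratification factors that vary within PDAC: fistula risk and biliary stent.

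Report the hazard ratio with its confidence interval. Keep the Kaplan-Meier curves and the log-rank test as the unadjusted companion.

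The cost is a few lines in the SAP, with no new visits or patients. CA19-9 is an eligibility requirement but is not named in the article's list of baseline data, so check that the value itself is entered in the database. The small downside is the need for a rule for missing CA19-9 and a check of proportional hazards, both to be written before outcome data are seen.

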### Trial monitoring: quality and safety plan

Participating surgeons in the PORTAL trial have significant experience in both open and robotic pancreatic resections: all have at least 10 years of very high-volume open pancreatoduodenectomy (> 100 annually), have significant experience in laparoscopic pancreatectomy, and have implemented a robotic approach in pancreatic resections for more than 5 years. Regarding RPD, all participants in the trial have undergone formal robotic training via proctoring, official daVinci® training course, and video training and have subsequently performed > 30 RPD each. Therefore, they have passed the learning curve for RPD [10], and reported outcomes on mortality and morbidity are in line with the literature and comparable with the open approach. All procedures are also performed in very high-volume centers for pancreatic surgery (> 100 open and > 20 robotic cases annually). Cumulatively, all participating centers have performed approximately 1000 RPD. Furthermore, for safety monitoring purposes, all operations will be recorded and reviewed in retrospect to assess for technique optimization and evaluate major incidents that have led to conversion and/or significant patient morbidity. The safety of the robotic approach will be evaluated in standardized intervals by the appointed institutional ethics and data monitoring committees, which will advise regarding the trial’s status. More specifically, 30-day mortality will be monitored independently in each arm, and if a safety threshold of 5% is reached at any given time, the trial will be withheld for further safety evaluation and potential decision for early termination. If deemed necessary, major protocol modifications will be approved by the ethics committee and will be communicated to participating centers.

### Financial considerations

Patients enrolled in the PORTAL trial will receive no compensation for their participation. Additionally, they will not need to cover medical costs applied for randomization in the RPD arm. Costs of the robotic equipment will be covered cooperatively by the patients’ insurance companies and the trial sponsors. This trial is partially funded by Intuitive Surgical, which explicitly has no role in the study design and/or data collection and interpretation.

## Discussion

The main goal of the PORTAL trial is to prospectively assess the feasibility and safety of RPD in patients with benign and malignant lesions of the pancreatic head and periampullary region and further compare it with OPD. This protocol describes the study design and presents the analyses that will be published after the conclusion of the trial. The comparison/control group of OPD was selected because it is the standard of surgical practice and has a proven safety record when performed in high-volume centers.

The feasibility and safety of RPD have so far been exhibited only in retrospective series of high-volume institutions. Zureikat et al. initially reported comparable 30-day morbidity and 90-day mortality rates between RPD and OPD [12], and similar results were also shown in recent meta-analyses [26, 27]. Moreover, data from Ruijin Hospital, the leading institution in the PORTAL trial, similarly demonstrated a 2.1% 90-day mortality in patients who underwent RPD [9]. The ongoing integration of minimally invasive and specifically the robotic approach in pancreatic surgery led to the development of evidence-based consensus guidelines and recommendations [15, 28]. Two main key points were highlighted: [1] there is no evidence to suggest superiority of robotic approach in pancreatoduodenectomy, due to lack of prospective randomized trials, and [2] RPD should be utilized in high-volume centers for pancreatic and minimally invasive surgery that have surpassed the learning curve. The significance of patient volume and learning curve in RPD has been previously underlined and associated with improvement in patient outcomes. Adam et al. defined a minimum number of 22 minimally invasive pancreatoduodenectomies per year to correlate with the decrease in postoperative complications [29]. Similarly, passing the learning curve in RPD was associated with improved morbidity and mortality rates as well; the number of RPD cases that constitute the learning curve has been previously identified to be at least 40 cases as an individual surgeon up to 250 cases within a single institution [8, 11, 30, 31]. All participating centers in the PORTAL trial are considered high-volume centers in pancreatic surgery and MIS and have surpassed the learning curve in RPD; therefore, the PORTAL trial is characterized as a phase 3 trial.

This study was designed as a non-inferiority trial, and the rationale for this decision was based on the lack of robust retrospective data to demonstrate the superiority of RPD versus OPD, regarding functional recovery. The goal is to prospectively examine the outcomes in RPD and demonstrate non-inferiority of this approach compared to OPD. Furthermore, the decision to focus on RPD only and not include laparoscopic pancreatoduodenectomy patients was multifactorial: the robotic platform offers extra degrees of freedom and improved surgical ergonomics and was previously found to have an advantage compared to the laparoscopic approach [32]. Additionally, LEOPARD-2, a prospective randomized trial comparing LPD versus OPD, failed to demonstrate the superiority of LPD in functional recovery, but most importantly, the minimally invasive arm was associated with more complication-related deaths and the study was terminated early for safety purposes [6]. These results have revealed both the significance of the learning curve and surgical experience in MIS.

The number of enrolled patients in the PORTAL trial is 244 and was calculated taking under consideration three main protocol parameters: [1] conversion to open surgery in the RPD arm, which was defined as 10% based on historical institutional data [2]; intraoperative findings of occult abdominal metastatic disease; and [3] loss to follow-up, which in randomized controlled trials where included patients are closely monitored is approximately 3% [33]. The selection of eligible patients was limited to upfront resectable lesions without the involvement of major vessels. RPD with vascular resection or in patients with PDAC who previously underwent neoadjuvant are being performed in the participating institutions in increasing numbers, and recent reports have demonstrated their safety and feasibility [34, 35]. However, the technical challenges encountered in these patients would considerably affect the studied outcomes. All participating institutions are national referral centers and are considered very high volume in terms of open and robotic pancreatic surgery. Considering the number of patients that are being reviewed on a daily basis, we expect no delays in patient recruitment via an initial approach at the outpatient clinic preoperatively.

The primary endpoint of this study is functional recovery, which is a more objective evaluation of recovery and combines postoperative complications and patient-reported quality of life (QoL) outcomes. It is determined by four main parameters in the immediate postoperative period: sufficient pain control, nutritional competency, mobilization, and no evidence of ongoing inflammation [36]. Indeed, these criteria are of main interest in all patients and remain the focus of conversation during preoperative decision-making: when will the patient be able to resume his daily activities. Moreover, patient-reported outcomes are widely accepted and incorporated in patient care [37, 38]. Additionally, the concept of functional recovery is separate from inelastic variables, such as postoperative complications and/or postoperative length of hospital stay [39]; different healthcare systems around the world have different capacities for patient care management in the community [40]. However, postoperative complication rate and severity, and length of stay will be compared between RPD and OPD as secondary endpoints. The established EuroQoL Group 5-level EQ-5D questionnaire was utilized for the assessment of the quality of life [https://euroqol.org/eq-5d-instruments/]. Similar to previous randomized trials comparing minimally invasive and open surgery [41], patient blinding is being applied to reduce bias due to patient expectations and limit the effect of psychological factors associated with either of the two surgical approaches [42].

The second primary endpoint of this study is the timing of adjuvant chemotherapy initiation in patients with pancreatic adenocarcinoma, who represent the main bulk of pancreatoduodenectomies. The role of chemotherapy in PDAC has been long established, and different regimens have been identified to provide survival benefits [43, 44]. A recent retrospective study by Girgis et al. demonstrated that long-term oncological outcomes in patients with PDAC who undergo RPD are borderline superior compared to the open approach [45]. These results differentiate from a large study on cervical carcinoma that showed inferior overall survival in the minimally invasive group [46]. Thus far, no prospective data exist to support non-inferiority of RPD regarding oncological outcomes. The optimal time for chemotherapy treatment in the postoperative setting in PDAC has been identified to be no later than 12 weeks in order to achieve a combination effect of local and systemic treatments, yet most oncologists aim to start at 8 weeks [47]. Based on institutional data, we identified the percentage of patients who initiate adjuvant chemotherapy to be approximately 50% in OPD and 75% in RPD, and we aim to compare the two groups and assess for the superiority of RPD (64 patients in each arm). Furthermore, we will compare the recurrence-free survival and overall survival between the two groups, as well as the patterns of recurrence which are closely associated with long-term outcomes in PDAC [48].

Secondary endpoints of the PORTAL trial include perioperative and long-term outcomes. A recent meta-analysis [27] and smaller retrospective series within the past few years have demonstrated significantly lower overall complication rates in RPD compared to the open approach, as well as benefits in terms of estimated intraoperative blood loss. Additionally, retrospective data on RPD in PDAC patients have shown increased R0 resection rates and higher numbers of harvested lymph nodes [27, 49] and no difference in recurrence-free and overall survival [50]. The targeted analysis of PDAC patients within the PORTAL trial will be able to answer the question of long-term oncological outcomes in RPD. Moreover, a comprehensive cost analysis will include and compare operative charges, postoperative institutional expenses, and potential readmission costs to identify in detail the presence—or lack thereof—of the economic burden of robotics utilization in pancreatoduodenectomy [51].

In conclusion, the primary goal of the PORTAL trial is to study the short-term and long-term outcomes in RPD, compare them with the established OPD, and provide high-level evidence regarding the value of the robotic approach in pancreatoduodenectomy. Proof of non-inferiority may allow wider implementation of RPD in high-volume centers and engage for further studies focusing on more complex robotic pancreatic surgery. The goal is to publish the results of the trial in a high-impact peer-reviewed journal.

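### The protocol says the PDAC sub-cohort will settle the long-term oncological question, but 128 patients followed for 2 years cannot exclude a survival hazard ratio of about 1.4 to 1.7 even if the arms look identical

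*Protocol article*

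**What the plan says.** The Discussion makes a direct statement about what the planned analysis can achieve: "The targeted analysis of PDAC patients within the PORTAL trial will be able to answer the question of long-term oncological outcomes in RPD". The paragraph before it observes that no prospective data yet support oncological non-inferiority of robotic pancreatoduodenectomy (RPD), and cites a study in another cancer in which overall survival was worse after minimally invasive surgery.

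The design behind the statement is as follows.

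- **Size.** From the Abstract: "A sub-cohort of 128 patients with pancreatic adenocarcinoma (PDAC) will also be compared". The only basis given is the chemotherapy endpoint, in Statistical considerations and analysis: "Institutional empirical data demonstrate that 50% and 75% of patients who undergo OPD and RPD, respectively, are eligible for adjuvant chemotherapy at 8 weeks", and then "With the same power and significance level as in the ITT group, 64 patients with pancreatic adenocarcinoma will be included in each arm".
- **Follow-up.** Patients in this sub-cohort "will be followed up for a period of 2 years after surgery, or until their time of death within this period".
- **Analysis.** Survival is estimated by Kaplan-Meier and "compared between the groups with the log-rank test".
- **Status.** Recurrence-free survival (RFS) and overall survival (OS) are secondary outcomes (Abstract and Table 2). No survival margin, target HR, expected number of events or power is stated for them. The trial's only non-inferiority margin, 1 day, concerns functional recovery.

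**The concern.** The open question, as the Discussion itself describes it, is whether the robotic approach costs patients survival. Answering it means excluding a detriment of some stated size, and that depends on the number of events. The sub-cohort was sized for a difference of 25 percentage points in a binary outcome at 8 weeks, which says nothing about precision for survival at 2 years.

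The protocol's conclusion says the trial will provide high-level evidence on short-term and long-term outcomes, and that proof of non-inferiority may lead to wider use of RPD. A reader could carry the non-inferiority finding for recovery over to survival if the survival comparison is non-significant and the Discussion has said in advance that this comparison will answer the question.

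**Working it through.** **1. Reproduce the plan's own figure.** Inputs from Statistical considerations and analysis: 50% versus 75%, 80% power, 5% significance, 1:1 allocation. With the usual two-proportion formula, two-sided and without continuity correction:

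n = [1.96 × √(2 × 0.625 × 0.375) + 0.8416 × √(0.25 + 0.1875)]² / 0.25² = (1.342 + 0.557)² / 0.0625 ≈ 58 per arm.

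With continuity correction it is 66. Two-sided Fisher's exact power at 64 per arm is 80.2%. So 64 per arm is reproduced as a sample size for the chemotherapy endpoint. (The main calculation is one-sided; a one-sided version here would need 46, or 54 with correction. This does not affect the survival point.)

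**2. Precision for survival.** With 1:1 allocation and d events in total, SE(log HR) ≈ 2/√d. At an observed HR of 1.0 the 95% limits are exp(±1.96 × 2/√d). The protocol gives no event rate, so d is an assumption: 40% to 70% of 128 dead by 2 years (51 to 90 deaths), and 60% to 80% with an RFS event (77 to 102). The last row, with every patient having an event, needs no assumed rate.

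| Events d | Share of 128 | SE(log HR) | 95% limits at observed HR 1.0 | Power for HR 1.5, two-sided 5% | HR detectable with 80% power |
|---|---|---|---|---|---|
| 51 | 40% | 0.280 | 0.58 to 1.73 | 30% | 2.19 |
| 64 | 50% | 0.250 | 0.61 to 1.63 | 37% | 2.01 |
| 77 | 60% | 0.228 | 0.64 to 1.56 | 43% | 1.89 |
| 90 | 70% | 0.211 | 0.66 to 1.51 | 49% | 1.81 |
| 102 | 80% | 0.198 | 0.68 to 1.47 | 53% | 1.74 |
| 128 | 100% | 0.177 | 0.71 to 1.41 | 63% | 1.64 |

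The power column is also the chance that the upper 95% limit falls below 1.5 when the true HR is 1.

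**3. Events needed.** For HR 1.5 with 80% power, two-sided 5% (Schoenfeld): d = 4 × (1.96 + 0.8416)² / (ln 1.5)² = 31.40 / 0.1644 ≈ 191. At one-sided 5% it is 4 × (1.645 + 0.8416)² / 0.1644 ≈ 151. Both exceed 128 patients. HR 1.5 is a yardstick chosen here, since the protocol names no survival margin.

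**4. What such a limit means.** If 2-year survival after open surgery were 50% (assumed) and hazards proportional, an HR of 1.63 would correspond to 0.50^1.63 ≈ 0.32, that is, 32% after RPD.

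**5. Losses.** With the protocol's 5% loss to follow-up, 128 × 0.95 ≈ 121 patients remain, and the ceiling limit rises from 1.41 to exp(1.96 × 2/√121) ≈ 1.43.

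**The case against.** The strongest reply is that this is one confident sentence in a Discussion. RFS and OS are openly ranked as secondary, the text says plainly that 64 per arm was chosen for the chemotherapy endpoint, and unpowered secondary endpoints are normal. The remark on non-inferiority stands in the preceding paragraph, so the long-term oncological question could be meant broadly, covering recurrence, its site, RFS and OS. All of this is fair, and no criticism is made of leaving survival unpowered. It does not rescue the sentence: even on the broad reading, whether survival is worse is part of the question, and the sentence claims a capability that the design lacks.

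Two stronger readings are tempting and should be resisted. A reader might infer that the protocol commits in advance to treating a non-significant log-rank test as proof of no difference. It does not: there is no decision rule for survival, and a misreading is only a foreseeable risk. A reader might also infer that no interval estimate is planned. The article does not mention one, but hazard ratios and confidence intervals are commonly left to the statistical analysis plan, which is not shown. In any case, reporting them would not make the claim true, because they would be about as wide as the table shows.

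It is also right that the event rates and HR 1.5 are not protocol figures. The 128-event ceiling and the 191-event requirement do not depend on any assumed event rate.

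**Conclusion.** The point holds as a statement in the protocol that its own design contradicts. At an observed HR of 1.0, the data would remain compatible with an HR for death of up to 1.73 (51 deaths) or 1.51 (90 deaths), and with an HR for RFS of up to 1.56 to 1.47 (77 to 102 events). The ceiling of 128 events gives 1.41. These figures assume 1:1 allocation, proportional hazards and the usual large-sample variance; the event counts below the ceiling are assumptions.

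It would go too far to call the survival comparison uninformative. With an observed HR near 1, a doubling of the hazard would be excluded across the assumed range, which is of some value where no prospective data exist. The design can supply an estimate with that precision, but it cannot settle whether RPD is oncologically non-inferior. The functional recovery endpoint and the 8-week chemotherapy endpoint are unaffected.

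**What to change.** Replace the Discussion sentence by a statement that RFS and OS in the PDAC sub-cohort are exploratory secondary estimates, ideally with the expected number of events and the resulting width of the confidence interval.

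Beside the log-rank test, report the HR with its 95% confidence interval from a Cox model that includes the randomisation factors. In this sub-cohort these are in effect fistula risk and preoperative biliary stenting, since the third factor is the PDAC diagnosis itself. State that a non-significant result will not be read as equivalence or non-inferiority.

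The cost is a change of wording and one routine model on data already being collected, with no additional patients or follow-up. The downside is that the stated aim becomes less favourable.
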